### Eligibility and recruitment

Participants in this study are patients with COPD admitted to the Department of Respiratory Medicine, Affiliated Hospital of Jilin University. The inclusion and exclusion criteria are shown below.

Inclusion criteria:
① Hospitalized patients diagnosed with COPD according to the Global Initiative for Chronic Obstructive Lung Disease criteria② Patients with clear consciousness, stable vital signs, and the ability to cooperate③ Patients who have given informed consent④ Adult patients⑤ Patients with a sputum viscosity classified by the same person as grade II or grade III which is characterized by the loss of humidifying function in the upper respiratory tract, as well as the loss of the mucociliary transport function, and impaired expectoration [28]

Exclusion criteria:
① Presence of neuromuscular disease or terminal disease② Presence of asthma or other respiratory diseases③ History of thoracic and abdominal trauma and surgery④ Presence of skin infection at the site of contact⑤ Presence of a cardiac pacemaker, artificial stent, artificial valve, or heart failure⑥ Presence of acute exacerbation of COPD or on a rehabilitation program

Patients meeting inclusion and exclusion criteria will be invited to participate in our research. Informed consent will be obtained from each participant. The recruitment process will be handled by an independent caregiver who is not involved in other procedures at the Medical Center in Changchun, China.

### Groups

#### Intervention group: active cycle of breathing techniques combined with phonophoresis

These patients will receive both active cycle of breathing techniques and phonophoresis during the 1-week intervention period. The active cycle of breathing technique consists of three main components [15]: breathing control, a thoracic expansion exercise, and a forced expiration technique.

##### Breathing control

Patients sit comfortably in a chair and breathe normally using the lower chest.

##### Thoracic expansion exercise

The physical therapist rests one hand on the epigastrium and guides the patients to breathe slowly and deeply using the lower chest. This is followed by holding the breath for 2 s and breathing out fully. This is repeated two or three times before returning to breathing control.

##### Forced expiration technique

The physical therapist guides the patient to inhale deeply, while simultaneously contracting the abdominal muscles and keeping the mouth and throat open. The patient then holds their breath for 2 s followed by vigorous exhalation, making a “ha” sound to stimulate coughing. The patient then returns to breathing control until ready to begin another cycle. Within 1 week of the intervention, each patient in this group will receive the active cycle breathing technique twice daily administered by the same physical therapist.

The phonophoresis procedures were developed by respiratory physicians, rehabilitators, caregivers, and other stakeholders. In this study, they will be led by the same experienced respiratory physician in the hospital who will not be involved in the active cycle of breathing technique. The physician checks the equipment and prepares a sterile patch before starting. Next, acetylcysteine is placed onto the sterile patch. Patients are auscultated and marked by the same experienced respiratory physician to determine the location of sputum accumulation. The emitter and the patch with the liquid are then applied in the marked position. The frequency will be adjusted to 20 kHz, with a depth of 10 mm–150 mm and intensity of 0.8 W/cm^2^, and treatment will continue for 20 min. This procedure is performed twice a day during the intervention period. If the patient has skin burns or intolerance during the execution, stop the intervention immediately.

#### Comparison group 1: active cycle of breathing technique

Comparison group 1 will receive the same active cycle of breathing, composed of breathing control, the thoracic expansion exercise, and forced expiration, as the intervention group. This is also performed twice daily during the 1-week intervention period, for a duration of 20 min per cycle. These patients will receive mucolytic agents by inhalation.

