Both expectoration and reducing lung inflammation are necessary in treating COPD. Phonophoresis is a physical therapy technique that combines ultrasound and topical medications [18]. It has been proven to decrease inflammatory infiltration [19] through the absorption of ultrasonic energy and cavitation [20] and has been widely studied as a non-invasive method of medication administration [21]. There is ample evidence showing that phonophoresis is both more effective and leads to greater patient compliance [22] than conventional methods for administering medication. Recent studies have demonstrated the efficacy of phonophoresis in the treatment of acute calcific tendinitis of the shoulder [23], chronic nonbacterial prostatitis [24], and chronic rhinosinusitis [25], among other diseases. At present, COPD patients in the Medical Center in Changchun, China, mostly use inhalation therapy to dilute the sputum. We propose exploring the use of phonophoresis combined with active cycle of breathing techniques to relieve the respiratory symptoms of COPD patients, which may be more effective than the use of a single treatment. To our knowledge, there are no reports of the use of this combined therapy for COPD. The aim of this single-blind, three-arm, randomized controlled trial, therefore, is to investigate combining active cycle of breathing techniques and phonophoresis in treating patients hospitalized with COPD.

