## Methods

### Study design

This is a single-blind, three-arm, randomized controlled trial. The intervention group will receive active cycle of breathing techniques combined with phonophoresis and control group 1 will receive active cycle of breathing only, while control group 2 will receive phonophoresis only. By comparing these three groups, we hope to explore the benefits of a combined program, compared to a single intervention. For the three-armed trial [26], COPD patients will receive active cycle of breathing techniques during hospitalization. Because the mean length of hospital stay for COPD patients in our medical center is 1 week, the duration of the intervention in our study will be set at 1 week. The trial will be conducted at the Medical Center in Changchun, China. In line with the recommendations of the Protocol Items Recommendations for Interventional Trials (SPIRIT) guidelines [27], our research protocol has been registered with the China Clinical Trial Registration (ChiCTR1900028506) and has been approved by the Ethics Committee of Jilin University (2019122301). We expect to begin recruitment in December 2019 and end in June 2021. Any changes to the plan will be negotiated with trial participants and the ethics committee. A copy of the revised protocol will be sent to the patient involvement branch of the ethics committee to add to the Investigator Site File, and any deviations from the protocol will be fully documented using a breach report form.

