#### Comparison group 2: phonophoresis

The phonophoresis conductance instrument (NAVA-01TD) is used to administer the drug in the hospitalized COPD patients, using the same mucolytic agents that are used for the intervention group. The patients will undergo phonophoresis twice daily during the 1-week intervention period for 20 min each time.

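### Study design describes control group 1 as breathing technique only, but Groups also gives it an inhaled mucolytic, so the comparison with control 1 does not isolate what phonophoresis adds

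*Protocol article*

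**What the plan says.** Study design states that "control group 1 will receive active cycle of breathing only, while control group 2 will receive phonophoresis only". It gives the purpose of comparing the groups as "we hope to explore the benefits of a combined program, compared to a single intervention".

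The Groups section describes what each arm receives:

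- **Combination:** "These patients will receive both active cycle of breathing techniques and phonophoresis during the 1-week intervention period". The phonophoresis procedure, printed at the end of the Forced expiration technique subsection, names the drug and its placement: "Next, acetylcysteine is placed onto the sterile patch".
- **Comparison group 1:** the same breathing technique as the combination arm, and then "These patients will receive mucolytic agents by inhalation". The agent is not named.
- **Comparison group 2:** phonophoresis, "using the same mucolytic agents that are used for the intervention group".

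Inhaled drugs are mentioned in two other places. The Abstract background says the breathing technique needs the sputum thinned first, commonly with inhaled medicines whose effect may be limited. The Introduction says COPD patients at the centre "mostly use inhalation therapy to dilute the sputum". Neither statement assigns an inhaled drug to a trial arm.

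**The concern.** One control arm is described in two ways. A reader who relies on Study design takes the comparison with control 1 as a test of adding phonophoresis to the breathing technique. A reader who relies on Groups sees an arm that also receives a drug intended to thin sputum, and sees that the combination arm receives its mucolytic by phonophoresis instead.

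This matters most for sputum viscosity, which is the first primary outcome and the one named in Sample size. An inhaled mucolytic is given to act on that outcome. Under Study design, a null against control 1 would be read as phonophoresis adding nothing to the breathing technique. Under Groups, the same null would mean only that acetylcysteine by phonophoresis was not found better than the inhaled regimen. A positive result would be mislabelled in the same way.

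**Working it through.** The point has no figure of its own, so the check sets the arm descriptions side by side.

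**Step 1. What each arm receives, as described in Groups**

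| Arm | Breathing technique | Mucolytic by phonophoresis | Mucolytic by inhalation |
|---|---|---|---|
| Combination | Yes | Acetylcysteine | None stated |
| Control 1 | Yes | No | Yes, agent unnamed |
| Control 2 | No | Same agents as combination | None stated |

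**Step 2. What each comparison contains.** Write B for the effect of the breathing technique, P for acetylcysteine by phonophoresis and M for the inhaled mucolytic. Treat the effects as additive for illustration only.

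- Combination versus control 2: (B + P) − P = B. This is the breathing technique added to phonophoresis, which fits the stated aim.
- Combination versus control 1: (B + P) − (B + M) = P − M. This replaces one mucolytic regimen with another.
- The comparison implied by Study design: (B + P) − B = P. No pair of arms that includes control 1, as described in Groups, gives this.

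If the inhaled mucolytic helps, P − M is smaller than P, and a difference of zero is compatible with P and M being equal and both beneficial. The article gives no value for M, so the gap cannot be sized.

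**Step 3. The alternative reading.** Suppose inhaled mucolytics are background care in all three arms. Then combination versus control 1 is (B + P + M) − (B + M) = P, and the add-on interpretation holds. Combination versus control 2 is still B.

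**Step 4. Whether control 2 has the same problem.** It does not. The Introduction says: "Phonophoresis is a physical therapy technique that combines ultrasound and topical medications". A drug is therefore part of phonophoresis by definition. The breathing technique is defined in Groups by three physical components, none of which is a drug.

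**Step 5. Sample size.** The stated inputs (three-arm analysis of variance, effect size 0.4, alpha 0.15, 90% power) give 20 per arm, with power 0.905. That is 60 in total, and 60 / (1 − 0.20) = 75, which matches the plan. Nothing in this arithmetic uses the description of control 1, so correcting that description leaves 75 unchanged.

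**The case against.** The strongest defence is that the mismatch is one of loose wording. The word *only* can mean without the other study intervention. The Abstract presents sputum thinning, usually by inhaled drugs, as a prerequisite of the breathing technique, so the technique with inhaled dilution could be its ordinary form. Groups discloses the inhaled mucolytic openly. The Introduction and Discussion already set phonophoresis against conventional drug delivery. The planned conclusion is only that the combination, if effective, may be a better treatment, and the analysis section names no separate control 1 contrast.

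Much of this stands. It lowers the weight of the point and shows that the comparator is reasonable. It does not remove the discrepancy: the Abstract and Introduction describe general practice and assign nothing to an arm, and the combined-versus-single aim still does not describe the control 1 comparison as the arms are written.

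Three stronger readings are tempting, and the document supports none of them:

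- **That the comparison with control 1 is invalid, or that the treatments must change.** Acetylcysteine by phonophoresis against a usual inhaled regimen is a legitimate comparison. The fault is in how Study design labels it.
- **That the other two arms certainly receive no inhaled drug.** The article does not say this. Inhalation is the prevailing practice at the centre, and a condensed article may leave concomitant care to the full protocol.
- **That the comparison isolates route of delivery.** The inhaled agent is unnamed, so drug as well as route may differ.

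**Conclusion.** The point holds as a contradiction about one control arm and about what one main comparison can show. As the arms are described, combination versus control 1 estimates acetylcysteine by phonophoresis against an unnamed inhaled mucolytic, with the breathing technique in both arms.

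The contradiction between Study design and Groups is plain in the text. The substitution reading is conditional: it rests on inhaled mucolytics being given to control 1 alone, which is what Groups states but which undisclosed background care could overturn.

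The size is interpretive. Power, sample size, treatments and analysis are not affected. It is worth correcting because the reading of a result on sputum viscosity depends on it and the correction is nearly free.

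**What to change.** The sponsor knows which situation applies and should make the matching change.

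- **If only control 1 inhales mucolytics:** in Study design, define control 1 as breathing technique plus inhaled mucolytic. State the two comparisons separately: against control 1, acetylcysteine by phonophoresis versus the usual inhaled mucolytic regimen on a breathing-technique background; against control 2, the breathing technique added to phonophoresis. Limit the control 1 conclusion accordingly, and make no claim about route alone unless the inhaled agent is also acetylcysteine.
- **If all three arms inhale mucolytics as background care:** say so in the arm descriptions under Groups. The comparison with control 1 can then be read as adding phonophoresis.

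The cost is one or two sentences in Study design, or one in Groups. Trial status says recruitment is under way, and neither change affects it. The downside of the first option is a narrower conclusion for one comparison.

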#### Comparison group 2: phonophoresis

The phonophoresis conductance instrument (NAVA-01TD) is used to administer the drug in the hospitalized COPD patients, using the same mucolytic agents that are used for the intervention group. The patients will undergo phonophoresis twice daily during the 1-week intervention period for 20 min each time.

### Outcome measurements

Outcome measures will be collected and analyzed by researchers blinded to the patients’ group allocation. All assessments will be performed at the commencement of the study and after the 1-week intervention, with the exception of assessments for sputum production and certain additional secondary outcomes (Fig. 1). Sputum production will be assessed after the 1-h intervention session and every 24 h during the week-long intervention period. Additional secondary outcomes will be collected only at the conclusion of the intervention. A summary of the outcome measures for the study is outlined in Table 1.

**Fig. 1 Fig1:**
[figure not shown]
The profile of the outcome measures for the study

**Table 1 Tab1:**
[figure not shown]
Time points of our research

*ACBT* active cycle of breathing technique, *FEV1%* forced expiratory volume in 1 s to the forced vital capacity, S*pO*_*2*_ arterial oxygen saturation, *CAT scale* COPD Assessment Test scale, *AIR scale* Anxiety Inventory for Respiratory Disease scale, *t*_*−1*_ enrolment, *t*_*0*_ baseline, *t*_*1*_ 1 week, *t*_*2*_ intervention close-out, *t*_*3*_ discharged

#### Primary outcomes

The first primary outcome will be sputum viscosity calculated using a viscometer [29, 30]. After the collection of sputum from patients, in line with the instructions, the assistant will insert the sputum into the rotor in the viscometer and read the digital output. The sputum viscosity is calculated by the formula (sputum viscosity = viscometer reading × 10). Patients will be given calibrated containers [31] at the baseline visit and instructed to collect 24 h worth of sputum in the container, between 07:00 each morning and 07:00 the following morning. The outcome assessor will observe and record the volumes of sputum at the 1- and 24-h time points daily during the intervention period.

We hope to reduce obstruction by clearing the sputum in the respiratory tract. Therefore, we will use the same pulmonary function meter to perform a complete spirometry assessment before and after the intervention [32]. Vital capacity can reflect the obstruction of pulmonary function and airway obstruction will be determined by FEV_1_%. The relation between expiration in the first second of forced expiration (FEV_1_) and the full forced vital capacity (FVC) will be represented by FEV_1_%, with normal values being approximately 75%. Generally speaking, the FEV_1_% of COPD patients is less than 70%. We are investigating whether this can be improved. The outcome assessor will only record vital capacity and FEV_1_% from the spirometry. We will follow the recommendations of the American Thoracic Society and European Respiratory Society [33] in the lung function test. Patients will be assessed between three and eight times, and the three best measurements with variability of less than 5% or 200 ml will be recorded [34]. The oxygen saturation of COPD patients will be expressed as SpO_2_. Similarly, SpO_2_ will be determined by pulse oximetry from the right middle finger [35–37] before and after the intervention. Since SpO_2_ is also a variable parameter, the patient will receive three evaluations and the average of the results recorded.

#### Secondary outcomes

The COPD Assessment Test scale (CAT scale) is a simple tool for assessing the health-related quality of life in COPD patients and is the recommended questionnaire in the global strategy for the diagnosis, management, and prevention of COPD [38]. Higher scores indicate a poorer outcome [39, 40]. The scale consists of eight points. Anxiety in patients with COPD will be assessed by the Anxiety Inventory for Respiratory Disease scale (AIR scale) [41]. The scale has ten points (score range, 0 [best]–30 [worst]), and a score of greater than eight indicates a high level of anxiety [42].

#### Additional secondary outcomes

Patient self-satisfaction, degree of cooperation, and the length of hospital stay will be additional secondary outcomes. Improvement in the patients’ condition, as well as their perception of the effectiveness of the interventions, will be evaluated by self-report on a scale of 0 to 100. After the intervention, the patients’ self-satisfaction will be scored on a 5-point Likert scale with 0 indicating “dissatisfied” and 4 meaning “very satisfied.” In addition, the proportion of patients who complete treatment during the study period will be used as the measure of their degree of cooperation [43]. These statistics will be compiled in the absence of the patient. The length of hospital stay will be measured in days [44].

### Sample size

Since the trial was designed with three arms, analysis of variance was chosen to calculate the sample size. We will have 90% power at the significance level (alpha) of 0.15 with an effect size of 0.4 to detect significant differences in sputum viscosity. Based on previous studies [45, 46], we assume that the dropout rate of our trial will be about 20% after the week-long intervention. Thus, the total sample size was 75, with 25 patients in each of the three groups. The sample size was calculated using the software PASS 2019.

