**Methods and analysis:**

We propose a single-blind randomized controlled trial using 75 hospitalized patients diagnosed with COPD with excessive sputum production. The patients will be divided into three groups. The intervention group will receive active cycle of breathing techniques combined with phonophoresis. The two comparison groups will be treated with active cycle of breathing techniques and phonophoresis, respectively. The program will be implemented daily for 1 week. The primary outcomes will be changes in sputum viscosity and production, lung function, and pulse oximetry. Secondary outcomes include the assessment of COPD and anxiety, measured by the COPD Assessment Test scale and the Anxiety Inventory for Respiratory Disease, respectively; self-satisfaction; the degree of cooperation; and the length of hospital stay. All outcome measures, with the exception of sputum production and additional secondary outcomes, will be assessed at the commencement of the study and after 1 week’s intervention. Analysis of variance will be used to investigate differences between the groups, and a *p*-value of less than 0.05 (two-tailed) will be considered statistically significant.

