### Data collection, management, and analysis

All patients’ data will be recorded by trained clinical researchers using a standardized case report form (CRF) and saved using the EpiData electronic database. To ensure the reliability of our study, the management of this trial will be conducted by the Trial Steering Committee (TSC). Main investigators and statisticians consist of our Trial Steering Committee, who will oversee the entire trial. Meetings will be held once a month to monitor the progress of the research and to share opinions when there are problems. The measurement data will be expressed by mean ± SD, and the count data will be expressed by frequency and percentage. A Kolmogorov-Smirnov test will be performed to analyze sample normality. Within-group changes in sputum viscosity, FEV_1_%, vital capacity, arterial oxygen saturation, quality of life, and the level of anxiety will be compared using a paired *t*-test or Wilcoxon test depending on the data distribution. Inter-group differences between baseline and post-intervention among the outcomes will be compared by one-way analysis of variance. According to the normality of the data distribution, a general linear model or multi-generalized linear model will be used to compare the differences between the primary and secondary outcomes after adjusting the covariates, including sociodemographic variables, such as sex, age, body mass index, smoking history, severity of disease, among others, and baseline variables. In addition, we will follow the principle of intention to treat (ITT) and use the sequence mean method to deal with the missing data to analyze the results of the comparison between groups of each outcome. To assess whether the missing data will affect the results of the study, we will compare participants who did not complete the intervention with those who completed the intervention to verify the sensitivity of the results of the trial. A two-tailed *p*-value of < 0.05 will be taken as significant. The data from this experiment will be entered by Epidata3.1 and analyzed by SPSS 26.0 software.

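### The trial is sized at alpha 0.15 but will be tested at 0.05, so the stated 90% power is about 78% with the planned dropout and 87% with none

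*Protocol article*

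**What the plan says.** The Sample size section explains the choice of method: "Since the trial was designed with three arms, analysis of variance was chosen to calculate the sample size". It gives the planning values, for differences in sputum viscosity, as "90% power at the significance level (alpha) of 0.15 with an effect size of 0.4". It then allows for losses ("we assume that the dropout rate of our trial will be about 20% after the week-long intervention") and concludes that "the total sample size was 75, with 25 patients in each of the three groups".

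The significance level for the analysis appears in two other places, and they agree with each other. The section on data collection, management, and analysis says that a two-tailed p-"value of < 0.05 will be taken as significant". The abstract, under Methods and analysis, says that a p-"value of less than 0.05 (two-tailed) will be considered statistically significant". The analysis section also names one-way analysis of variance for the between-group comparisons. The sizing and the analysis therefore use the same kind of test and differ only in the significance level.

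**The concern.** A power figure describes a test at a given significance level. A test at 0.15 rejects more readily than one at 0.05, so 90% power at 0.15 cannot also be the power at 0.05 for the same patients and the same effect. The article gives no reason for sizing at a level three times the one it will use.

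Sputum viscosity is the first primary outcome and the only outcome with a power statement. If its result is not significant, readers will judge it against a claimed 10% risk of missing the assumed effect, and the actual risk is higher. There is also a smaller risk in the other direction: a reader could take 0.15 as the decision level for viscosity, which would triple the false-positive rate set in the analysis section.

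**Working it through.** **Inputs**

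| Quantity | Value | Source |
|---|---|---|
| Test | one-way ANOVA, 3 groups | Sample size; analysis section |
| Effect size | 0.4, read as Cohen's f | Sample size (type not named) |
| Planned power | 90% | Sample size |
| Alpha for sizing | 0.15 | Sample size |
| Alpha for analysis | 0.05 | Abstract; analysis section |
| Dropout | 20% | Sample size |
| Total | 75, 25 per group | Sample size |

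**Formula.** For the overall F test with N evaluable patients in three equal groups, the degrees of freedom are 2 and N − 3, and the noncentrality is λ = N × f² = 0.16 × N. Power is the probability that a noncentral F with this λ exceeds the central F critical value at the chosen alpha. The dropout allowance is N/(1 − 0.20).

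**Step 1: reproduce the stated 75.** At alpha 0.15:

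- 19 per arm: N = 57, λ = 9.12, power 89.1% (too low).
- 20 per arm: N = 60, λ = 9.60, critical F about 1.96, power 90.5% (sufficient).
- Dropout: 60/0.80 = 75, or 25 per arm. This matches exactly.

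**Step 2: could 0.15 be a misprint?** The same calculation with other inputs gives:

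| Alpha | Power | Per arm | Evaluable | Total after 20% dropout |
|---|---|---|---|---|
| 0.15 | 90% | 20 | 60 | **75** |
| 0.10 | 90% | 23 | 69 | 87 |
| 0.05 | 90% | 28 | 84 | 105 |
| 0.05 | 80% | 22 | 66 | 83 |
| 0.015 | 90% | 36 | 108 | 135 |

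Of these, only 0.15 returns 75, so 0.15 was the value used. The exact match also supports reading 0.4 as Cohen's f and the allowance as division by 0.80.

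**Step 3: power at 0.05 with f = 0.4**

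| Evaluable | Loss from 75 | λ | Critical F | Power | Type II error |
|---|---|---|---|---|---|
| 60 | 20% | 9.60 | 3.16 | 77.6% | 22.4% |
| 66 | 12% | 10.56 | 3.14 | 81.8% | 18.2% |
| 69 | 8% | 11.04 | 3.14 | 83.7% | 16.3% |
| 75 | 0% | 12.00 | 3.12 | 86.9% | 13.1% |

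**Step 4: what 90% power at 0.05 would take.** With f = 0.4, it takes 28 per arm: N = 84, power 90.7%, and 84/0.80 = 105 randomised (35 per arm). With 60 evaluable patients, 90% is reached only for f of about 0.47.

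**The case against.** - **Dropout may be low.** The Discussion says that losses are unlikely to be high in an inpatient study, and the earlier trials it cites lost 10% to 18.75%. The 77.6% figure belongs to the full 20% dropout, and a type II error of more than double the stated 10% applies only there. This stands as a reason to give a range. It does not rescue the claim, because power is 86.9% even with no losses, and 20% is the protocol's own planning figure.
- **The planned adjusted model could recover power.** The analysis section also foresees a linear model with baseline covariates. The documents give no correlation between covariates and outcome. If f = 0.4 refers to the unadjusted outcome, assumed correlations of 0.3, 0.5 and 0.6 with a single covariate give about 82%, 89% and 93% power at 60 evaluable. So the 78% describes the unadjusted ANOVA only. But the stated 90% is also an unadjusted figure, and the Sample size section claims no gain from adjustment.
- **Intention to treat with mean imputation keeps 75 in the analysis.** It keeps the count, but imputed means add no information.
- **The alpha is printed beside the power.** A careful reader is therefore warned, and the 0.05 rule governs inference in any case, so the type I error of the test is not affected. This is correct. The fault is a misstated power claim and an inconsistency between sections, not a slip in calculation.

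Sidedness offers no way out either, since the overall F test has no one-sided or two-sided form.

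**Conclusion.** The concern holds. The 75 patients follow from a test at 0.15, and the trial will test at 0.05. At that level the unadjusted three-group ANOVA on sputum viscosity has 77.6% power with the planned 60 evaluable patients and 86.9% with all 75, so the stated 90% is not reached anywhere in that range. At the planned dropout the type II error is 22.4%, against the stated 10%.

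These figures assume that 0.4 is Cohen's f, that the groups are equal in size, and that the test is the overall F test on this one outcome. They make no allowance for pairwise comparisons between arms or for the several primary outcomes, which could only lower the power if alpha were split among them.

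**What to change.** Keep 75 patients and the 0.05 level, and amend the Sample size section so that the power is stated at 0.05. Suggested wording:

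> *With 60 evaluable patients (75 less 20% dropout), a one-way ANOVA at alpha 0.05 has about 78% power for Cohen's f = 0.4 in sputum viscosity, and about 87% if all 75 are evaluable. With 60 evaluable patients, 90% power corresponds to f of about 0.47.*

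Alpha 0.15 should no longer appear as the trial's significance level. The amendment record can note that 75 was originally derived at that level, so that the basis of the number stays traceable.

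The cost is a short amendment and a less favourable power statement. No analysis changes and no extra patients are needed, which matters because recruitment has begun. If the sponsor instead wants to keep the 90% claim for f = 0.4 at 0.05, that would take 105 randomised patients, which is 30 more than planned.
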